# Investigating the effects of indoor lighting on measures of brain health in older adults: protocol for a cross-over randomized controlled trial

**DOI:** 10.1186/s12877-023-04594-7

**Published:** 2024-10-11

**Keywords:** Brain health, Cognitive function, Healthy aging, Indoor lighting, Physical activity, Sleep, Social engagement

## Abstract

**Background:**

The worldwide number of adults aged 60 years and older is expected to double from 1 billion in 2019 to 2.1 billion by 2050. As the population lives longer, the rising incidence of chronic diseases, cognitive disorders, and behavioral health issues threaten older adults’ health span. Exercising, getting sufficient sleep, and staying mentally and socially active can improve quality of life, increase independence, and potentially lower the risk for Alzheimer’s disease or other dementias. Nonpharmacological approaches might help promote such behaviors. Indoor lighting may impact sleep quality, physical activity, and cognitive function. Dynamically changing indoor lighting brightness and color throughout the day has positive effects on sleep, cognitive function, and physical activity of its occupants. The aim of this study is to investigate how different indoor lighting conditions affect such health measures to promote healthier aging.

**Methods:**

This protocol is a randomized, cross-over, single-site trial followed by an exploratory third intervention. Up to 70 older adults in independent living residences at a senior living facility will be recruited. During this 16-week study, participants will experience three lighting conditions. Two cohorts will first experience a static and a dynamic lighting condition in a cluster-randomized cross-over design. The static condition lighting will have fixed brightness and color to match lighting typically provided in the facility. For the dynamic condition, brightness and color will change throughout the day with increased brightness in the morning. After the cross-over, both cohorts will experience another dynamic lighting condition with increased morning brightness to determine if there is a saturation effect between light exposure and health-related measures. Light intake, sleep quality, and physical activity will be measured using wearable devices. Sleep, cognitive function, mood, and social engagement will be assessed using surveys and cognitive assessments.

**Discussion:**

We hypothesize participants will have better sleep quality and greater physical activity during the dynamic lighting compared to the static lighting condition. Additionally, we hypothesize there is a maximal threshold at which health-outcomes improve based on light exposure. Study findings may identify optimal indoor lighting solutions to promote healthy aging for older adults.

**Trial registration:**

ClinicalTrials.gov Identifier: NCT05978934.

## Background

According to the World Health Organization (WHO), the worldwide number of adults 60 years and older is expected to double from 1 billion in 2019 to 2.1 billion in 2050 [1]. As the population lives longer, the incidence of chronic diseases, cognitive disorders, and behavioral health changes will increase and negatively impact each adults’ health span. Although many age related health conditions are non-modifiable, certain lifestyle behaviors can help maintain or improve the brain and functional health of older adults as they age [2]. Regularly exercising and staying physically active has been shown to lower all-cause mortality in older adults [3, 4]. Sleep can also affect a multitude of health factors [5]. Poor sleep quality can impair cognitive performance [6] and increase the risk of dementia and all-cause mortality [7]. Socializing and staying mentally active are additional behaviors that can maintain or improve one’s brain health [8–11]. Adults who are socially isolated or lonely have been found to be at higher risk for heart disease, depression, and cognitive decline [12–16]. Thus, healthy lifestyle behaviors can increase older adults’ likelihood of remaining healthy later in life.

What can be done to promote such healthy lifestyle behaviors for older adults? One approach is to examine their day-to-day environment and determine whether modifying components of their living space may improve daily cognitive and physical stimulation. Indoor lighting could be a nonpharmacological approach to encourage healthy lifestyle behaviors that promote or maintain the brain health for older adults [17–19]. The importance of indoor lighting is often thought of in relation to seeing and performing activities. However, lighting has additional health-related benefits. For example, individuals who are exposed to more blue light during the daytime and less blue light during nighttime (e.g., dynamic lighting) often experience improvements in sleep quality [20–27]. This improvement in sleep quality could be due to increased suppression of melatonin secretion from the increased exposure to blue light in the morning, which helps entrain one’s circadian rhythm [28, 29]. Increasing the intensity of light in the morning also can improve the physical activity, cognitive function, and mood of adults exposed to the light [30–33]. Increasing the amount of ambient lighting in senior care facilities is also a preventative strategy to decrease fall risk [34]. However, there are saturation effects on subjective alertness and melatonin suppression when the light level reaches a certain threshold [35–39], and potentially negative effects such as increased agitation [40] or anxious/depressive behavior [41] if there is too much blue light exposure by people [42]. Thus, designing lighting systems specifically tailored for older adults’ residences is crucially important to promote their health and well-being and to improve their health spans.

Taking into consideration how older adults perceive light is crucial when designing indoor lighting systems to improve their health spans. Older adults need greater light intensities compared to younger adults to achieve health-related benefits [43–47]. Pupillary miosis and lens yellowing that occurs with age may explain the need for increased light intensities for older adults [48, 49]. Artificial light can be used to augment natural light as a therapy to improve sleep, mood, and general well-being [43]. Recent studies have shown that light therapy can significantly improve sleep disturbances, reduce agitation and depressive symptoms, and even enhance cognitive function in older individuals with dementia [50–55]. The efficacy of these natural light therapies may be due to activating intrinsically photosensitive retinal ganglion cells (ipRGCs), a subset of retinal ganglion cells in the eye that serve as the zeitgeber for the circadian system to regulate sleep-wake behavior [56–59]. However, activating ipRGCs outside of this pattern can increase the risk of developing circadian rhythm sleep-wake disorders, memory decline, and dementia [3, 43, 60, 61]. The timing, duration, brightness, and color of artificial light exposure have positive or negative effects on one’s physiological and psychological health [23, 35, 36, 62–75]. Understanding how the different lighting parameters positively or negatively affect the health of older adults is critical for improving their health span later in life.

This research protocol presents a novel approach to understanding how different indoor lighting conditions affect specific measures of brain health in older adults. Here, we are examining how three different lighting conditions affect measures of sleep quality, physical activity, cognitive performance, or social engagement by study participants. Our central hypothesis is each of these measures of brain health will increase when patients experience dynamic lighting conditions compared to static lighting conditions, because the health benefits of circadian lighting shown previously will subsequently improve sleep quality, cognitive performance, physical activity, and social engagement. To test our hypothesis, participants will each experience a dynamic and static lighting condition during which we will collect different measures related to their brain health. As a secondary hypothesis, we expect that the amount of blue light exposure saturates improvements in each measure of brain health, and we will examine this by comparing each measure of brain health between two different dynamic lighting conditions. Successful completion of this research protocol is expected to provide a better understanding about how measures of brain health of older adults could be improved by strategically designing the indoor lighting of their residences. Findings from this study could ultimately lead to optimal indoor lighting solutions and guidelines that maintain or improve the health and well-being of adults as they age.

## Methods/Design

### Ethical considerations

This study protocol involving human participants was reviewed and approved by The Mayo Clinic Institutional Review Board in March 2023, under the number 22-005400. Individuals will provide their written informed consent to participate in this study and this study. All experiments will be performed in accordance with relevant guidelines and regulations (such as the Declaration of Helsinki).

### Study aim

The purpose of this research study is to determine how indoor lighting affects different measures of brain and general health, such as sleep quality, physical activity, cognitive function, and social engagement, in older adults.

### Study setting

This study will be conducted in a senior living facility in Rochester, Minnesota, USA. Participants who live in the independent living residences, of which there are over 100 in the facility, will be recruited.

### Participants

Initially, up to 100 older adults will be screened into the study based on the inclusion exclusion criteria. However, because we are working with older adults where the incidence of cognitive impairment may be greater, we anticipate that up to 70 individuals will remain eligible after completing the consent capacity assessment (described below). Participants will be asked to allow study staff to install lighting in their residences that can be controlled remotely to produce the different lighting conditions. Up to 35 residences will be outfitted with the lighting systems resulting in between 35 and 70 participants being recruited (depending on whether the residence is single and double occupancy).

### Inclusion criteria

At least age 60;Able to wear wearable devices throughout the study;Willing to have their lighting in their kitchen and dining areas changed and controlled for the study;Willing to have environmental sensors placed in their residence;Willing to provide contact information about their primary care provider (PCP); and.Able and has capacity to provide informed consent (score > 14.5 based on UBACC consent capacity form).

### Exclusion criteria

Is legally blind.Previously renovated their living units and no longer have the standard lighting installation offered by the Senior Living Facility;Currently spend or plan to spend most of their day outside of their residence during the study (i.e., would not experience the indoor lighting intervention for the majority of the study);Plan to travel to a different time zone during the study; or.Plan to be away from their residence for more than a week during the study.

Recruitment procedures will include word of mouth, flyers, and emails. There will also be presentations by members of the study team to potential study participants at the senior living facility to help answer questions or help with recruitment via word of mouth. Interested individuals can reach out to the study team to learn more and determine if they are eligible for the study. Any interested individual will be asked to complete an initial eligibility assessment.

### Initial eligibility assessment

During the Initial Eligibility Assessment, interested individuals will be provided a brief screening survey to determine if they meet the basic inclusion/exclusion criteria of the study. This will be provided electronically via Qualtrics. Participants who are eligible will then be provided the consent form to start the consenting process. Because the population we are recruiting is comprised of older individuals, there is some risk of severe cognitive impairment and/or decline among eligible survey respondents. Therefore, it is necessary to ensure each participant has the capacity to fully understand the study procedures and requirements before signing the consent form. A modified version of the University of California, San Diego Brief Assessment of Capacity to Consent (UBACC) will be administered to every individual after completing the digital consent form by a Mayo Clinic research coordinator. The UBACC has demonstrated high sensitivity and specificity and is an all-around strong assessment of one’s ability to understand the consent document before signing [76]. The UBACC will be administered and scored based on the guidelines from Jeste et al. Participants will need to score greater than 14.5 to be eligible for the study (as outlined in the inclusion criteria above).

We expect most participants to be deemed capable of consenting via the UBACC. However, we have buffered the total number of participants to account for individuals who do not meet inclusion criteria based on UBACC scores. Such participants will be provided an email explaining that (1) the nature of this study involves sophisticated components of technology solutions, monitoring, and data collection and (2) due to this, selection of participants needs to meet criteria to maximize the quality of intervention delivered while ensuring full understanding and safety for all participants involved.

Upon passing the UBACC, participants will be assigned the next available participant ID from a sequential pre-populated list. This ID will have been pre-assigned in inventory to all participant-specific item serial numbers (e.g., wearable sensors, light bulbs, etc.). Participants will then be initially randomly assigned to cohort based on a random number sequence and finally these cohorts will be stratified by gender. The Mayo Clinic research coordinator, who will not be involved in data analysis or collection, will be responsible for assigning IDs to cohorts. Participants will be blinded to which cohort and condition they are in.

### Baseline assessment/survey

A baseline survey will be used to collect information about each participant’s demographics, education level, current medications, and/or socioeconomic status.

### Study design: cross-over study design with an exploratory third condition

The present study employs a two-arm, randomized, cross-over, single-site trial design. Participants will experience three 4-week lighting conditions (indicated as L1, L2, and L3 and described in the “Environmental Lighting Conditions” section to follow and depicted in Fig. 1). Cohort 1 will experience L1 followed by the L2 condition and cohort 2 will experience L2 followed by the L1 condition. Both cohorts will then experience the L3 condition. The primary outcome of this study is to determine how each lighting condition affects measures of sleep quality as assessed using wearable devices and self-report surveys. The secondary outcomes of this study are to determine how each lighting condition affects physical activity, cognitive function, social engagement, and mood as assessed using wearable devices, cognitive tasks, and self-report surveys. We will compare each of these measures between the L1 and L2 condition to test our central hypothesis that exposure to dynamic lighting (L2) will result in improvements of each measure compared to static lighting (L1). We will then compare these measures between L2 and L3 conditions to test our secondary hypothesis that improvements in measures of brain health saturate based on the amount of equivalent melanopic lux (EML) exposure.

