### Measures of brain health using wearable devices

The goal of this study is to assess how lighting affects different measures of brain health. Although we are not performing any neuroimaging to directly measure brain activity, we are able to use different wearable devices, cognitive assessments, and surveys to infer how measures of brain health change, including changes in participants cognitive, mental, and physical health. During each day of the study, physiological measures will be recorded using wearable devices. Heart rate, steps taken, and sleep quality will be measured using a wrist-worn smartwatch (Withings ScanWatch, Withings, France SA). Participants will be asked to wear the smartwatch when awake and asleep, except when needing to bathe, wash, or swim, or when they need to charge the device. Measurements that will be analyzed from the watch will include participants’ steps taken and heart rate throughout each day of the study. Under-the-mattress devices (Withings Sleep Tracking Mat) will also be used to monitor each participant’s sleep. In combination with the smartwatch, sleep measurements that will be analyzed will include participants’ total sleep time, wake after sleep onset, and sleep stages (deep sleep, light sleep, and probable REM sleep as reported by the device). Data from these devices will be synchronized using the Withings Health Mate App (Withings, France SA).

Participants will also wear a LYS light sensor (LYS Technologies LTD, Copenhagen, Denmark) to monitor the amount of light to which they are exposed each day. Each participant will wear the LYS sensor on their collar to best capture their personal light exposure as close to their eye level as possible. This device will capture their light exposure both within and outside of their residence. The LYS button will measure EML, illuminance (lux), and correlated color temperature (CCT) which will be compared across each day of the study. To ensure compliance that participants wear the device, we can monitor the recorded values remotely each day. Should the signals recorded have very low variance, we will use this as an indicator to have a member of the study team reach out to the participant to ensure they are wearing the device.

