Morningness Eveningness Questionnaire (MEQ)	Start of Baseline
Berlin Questionnaire	Start of Baseline
TIPI Big 5 Personality	Start of Baseline
Stanford Sleep Scale	Daily
SPANE	Daily
Groningen Last Night Sleep Report	Daily
DASS21	Weekly
PHQ-8	Weekly
UCLA Loneliness Scale	Weekly
Falls / Hospitalization Survey	Weekly
Lawton Brody Instrumental Activities of Daily Living Scale	End of Condition
Lubben Social Network Scale - Revised (LSNS-R)	End of Condition
End of Condition Survey	End of Condition
End of Study Opinion Survey	End of Study

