**Fig. 3 Fig3:**
[figure not shown]
Drawing of an example floorplan where the lighting intervention will be implemented. Measurements are taken in four directions at specific locations in the room. Example locations and directions are shown in blue. Each floor plan has built-in lighting fixtures in the ceiling as indicated by the orange circles. Additional floor lamps will be added to the room to increase the amount of light to which participants are exposed. For the L3 condition, the amount of blue light needs to be increased compared to the L2 condition. This will be accomplished by placing a tabletop lamp in the corner above the cabinets in the kitchen. Only the kitchen and dining areas will have the lighting system installed for this study, as these are where we anticipate participants will spend most of their time

We used this simulation approach to ensure that we could reach our minimum brightness levels. As shown in Fig. 4, we simulated the morning light scene from the L2 condition (6500 K, 280mlux) and the lighting system exceeded our target EML value of 280 mlux in the kitchen and dining areas overlapping where we anticipate a participant sitting. To achieve these EML values, we needed to include two floor lamps with 5-in-1 splitters to increase the amount of light emitted from each lamp (e.g., output from five Philips Hue dynamic light bulbs instead of one).

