### Statistical analysis plan

Using data from both wearable devices and surveys, the primary comparison will be within-person change in sleep quality scores between each of the three lighting conditions (L1, L2, L3) and the same scores measured during the baseline period. The L1 condition serves as an active control condition as this is the same lighting as they would typically experience in the baseline condition. The secondary comparison will be to compare changes in physical activity, heart rate, and survey data across each lighting condition pair. Data collected during the baseline period will also be compared against the L1 condition to determine whether asking participants to change their behavior with the lights (e.g., do not turn the lights off) affects any of the dependent variables of interest, thereby ensuring that any health benefits seen in the dynamic conditions relative to the static condition are likely reflective of improvements over participants lighting as usual. Participants who are eligible only because their partner is eligible will be analyzed separately.

We will use generalized estimating equations to account for the longitudinal repeated-measures design and handle missing data. For the surveys and cognitive assessments, there will be a minimum of 8 measurements per lighting condition (two cognitive assessments per week for four weeks). If only 35 participants are enrolled, we expect 80% power to detect a difference of minimum of 0.45 standard deviations. Conversely, if we have 70 participants enrolled (i.e., all the rooms are double occupancy with both persons eligible) we expect 80% power to detect a minimum difference of 0.3 standard deviations. For either of these scenarios, we expect to be able to detect at least 0.3 standard deviations, yielding sufficient power, even for the relatively infrequent cognitive assessments. To minimize missing data,, we will monitor key metrics (such as response rates) throughout the study using IRB-approved approaches to encourage participation. As a rule of thumb, participants who complete the study with greater than 50% missing data on any outcome measure will not be included in the relevant final analysis population.

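### The primary outcome is an unranked set of sleep measures and two sections give different primary contrasts, so no single test decides the trial; the participant-blinding statement also does not fit visibly different lighting

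*Protocol article*

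**What the plan says.** **Outcome.** The Study design section gives the primary outcome as the effect of each lighting condition on "measures of sleep quality as assessed using wearable devices and self-report surveys". The section on wearable devices names the device measures: "total sleep time, wake after sleep onset, and sleep stages (deep sleep, light sleep, and probable REM sleep as reported by the device". Table 1 adds two sleep scales collected daily, the "Groningen Last Night Sleep Report" and the "Stanford Sleep Scale". The other two sleep questionnaires, the Berlin and the Morningness Eveningness, are given only at the start of baseline and so cannot measure change.

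**Contrast.** The Study design section says: "We will compare each of these measures between the L1 and L2 condition to test our central hypothesis". It gives L2 against L3 to the secondary hypothesis. The Statistical analysis plan section, using both wearable and survey data, defines the primary comparison as within-person change in sleep scores "between each of the three lighting conditions (L1, L2, L3) and the same scores measured during the baseline period".

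**Blinding.** The Initial eligibility assessment section states: "Participants will be blinded to which cohort and condition they are in". On how L3 gets its extra light, the Fig. 3 legend says: "This will be accomplished by placing a tabletop lamp in the corner above the cabinets in the kitchen".

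**The concern.** A confirmatory trial needs one identifiable test, or a stated rule over several, that tells a reader whether the primary hypothesis was met. Here the measure is left open among several and the contrast differs between two sections. If results are mixed, for example total sleep time unchanged, deep sleep better and the Groningen score better, the article gives no basis for calling the trial positive or negative.

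The choice of contrast also affects validity. L1 against L2 is the comparison that the randomised cross-over protects. A comparison with baseline is before-after: baseline always comes first, lasts about two weeks instead of four, and lets participants use their lights as usual, whereas in the conditions they are asked to keep them on while awake. L2 or L3 against baseline therefore mixes the lighting with calendar time and the change in behaviour.

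The blinding statement matters because two of the candidate primary measures are self-reported.

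**Working it through.** **1. The plan's own figures.** The article gives no family-wise error. Its only quantitative statement is 80% power for 0.45 SD with 35 participants and 0.3 SD with 70. It states no significance level, sidedness or within-person correlation.

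- Two-sided 5%, paired, in SDs of the difference: (1.960 + 0.842)/√35 = 0.474 and 2.802/√70 = 0.335, against the stated 0.45 and 0.3.
- Both stated figures come within two points of 80% power only with an assumed correlation: about 0.59 for a two-sided paired t-test (power 81.5% and 78.0%), or about 0.48 one-sided (81.9% and 78.6%).

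The power statement is tied to no named sleep measure, so it does not show which test is primary. It neither supports nor weakens the point.

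**2. Count of candidate measures.** Device: total sleep time, wake after sleep onset, deep, light and probable REM sleep = 5. Daily self-report: Groningen and Stanford = 2. Total 7. No composite, ranking or success rule is stated. For light sleep the article gives no direction of benefit.

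**3. The two sections side by side.**

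| Section | Contrast | Purpose given | Randomised? |
|---|---|---|---|
| Study design | L1 vs L2 | central hypothesis | yes |
| Study design | L2 vs L3 | secondary hypothesis | no, L3 is always last |
| Statistical analysis plan | L1, L2 and L3, each vs baseline | primary comparison | no, before-after |

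**4. Family-wise error with independent tests.** Formula: 1 − 0.95^k, with 5% per test assumed.

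- Seven measures, L2 vs L1 only: 1 − 0.95^7 = 0.302.
- Seven measures, three baseline contrasts: k = 7 × 3 = 21, and 1 − 0.95^21 = 0.659.
- One measure, one contrast: 0.05.

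**5. Family-wise error with correlated tests.** Independence is not realistic: sleep stages are parts of total sleep time, and the three baseline contrasts share one baseline. With equal, independent errors, Var(condition − baseline) = 2σ² and Cov = σ², so two such contrasts correlate at 0.5. Simulating correlated normal test statistics (100,000 draws per setting, two-sided 5%, equal correlation between measures) gives, for seven measures:

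| Correlation between measures | L2 vs L1 only | Three baseline contrasts |
|---|---|---|
| 0.3 | 27.0% | 56.3% |
| 0.5 | 22.9% | 49.2% |
| 0.7 | 17.7% | 39.9% |
| 0.8 | 14.8% | 34.0% |

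**6. Blinding.** L1 has fixed colour and brightness and matches the existing lighting. L2 varies through the day, with a morning scene of 6500 K and 280 mlux. L3 raises the morning target to 500 mlux, using an added lamp with a 12,000-lumen bulb that is not part of L2. Participants also fill in a survey about each lighting condition. They may not know cohort labels or hypotheses, but they can tell static from changing light.

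**The case against.** Several counter-arguments carry weight.

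- **A contrast is named.** It would be wrong to infer that no contrast carries the central hypothesis: the Study design section assigns it to L1 vs L2, and the third condition is labelled exploratory. What stands is that the Statistical analysis plan section calls something else primary.
- **66% is not the trial's error rate.** It is an upper bound under independence, at a significance level that the article does not state. It also counts L1 vs baseline, which the article uses to check the behaviour change and not to test dynamic lighting. Counting only errors in a favourable direction, seven measures in one contrast give 1 − 0.975^7 = 16% if independent, and about 14% to 7% at correlations of 0.3 to 0.8. That presumes a favourable direction for every measure.
- **No any-one-wins rule is written.** A reader might infer that any single positive measure could be declared the primary result. The hypothesis speaks of every measure improving, which could mean that all must succeed and would not inflate error. But no such rule is stated either.
- **Multiplicity may be handled elsewhere.** A separate analysis plan may exist, so a missing adjustment is not itself a fault. The open measure and the conflicting contrast are, because this article fixes both.
- **Several measures are deliberate.** The Discussion explains that, without polysomnography, several sleep measures are used together. That justifies collecting them, not leaving all of them primary.
- **Blinding.** The article never says that blinding protects the self-report data, and self-report is two of seven measures. Whether the Stanford scale, which rates sleepiness, counts as sleep quality is a judgement. The extra lamp bears on L3 only. The static-versus-dynamic difference remains visible in L1 vs L2.

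**Conclusion.** The point holds in a limited form. The primary outcome is an unranked set of device and self-report sleep measures, and the two sections that define the primary contrast disagree, one of them choosing a non-randomised before-after comparison. For the randomised contrast alone, the chance of at least one false-positive sleep result is about 15% to 27% at correlations of 0.8 to 0.3, and at most 30%. If the three baseline contrasts are primary, it is about 34% to 56%, and at most 66%. These figures assume a two-sided 5% level per test, seven measures, equal correlations and no adjustment. They describe what the wording permits, not what the sponsor will necessarily do.

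The statement that participants are blinded to condition is contradicted by the lighting described. The consequence is possible expectation bias in the two self-report measures; device measures are less exposed. The documents do not support concluding that the whole primary outcome is compromised by unblinding.

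**What to change.** Before any outcome data are inspected:

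1. Reconcile the Study design and Statistical analysis plan sections so that the within-person L2 − L1 difference from the randomised cross-over is the primary comparison.
2. Name one device-measured sleep outcome, of the sponsor's choice, as the single primary test. Total sleep time or wake after sleep onset, averaged over the 4-week condition, are examples.
3. Make all other sleep measures, including self-report, secondary with an adjustment such as Holm, or label them supportive. Treat the baseline and L3 contrasts as secondary or exploratory.
4. Restate the blinding sentence: participants can see the lighting, and only what is actually withheld from them, for example the cohort label, is masked. Do not claim masked analysts unless this is put in place. The article does not state it, and the Data management section describes participant identifiers that show the cohort.

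The text changes are small, but the timing matters. Recruitment began in April 2023, so the change should be dated and justified; if outcomes have already been examined, the choice should be reported as made afterwards. The price is that the sponsor commits to one measure, and a result on any other becomes supportive.
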